**Methods:**

The study aims to monitor the implementation of a new digital communication assistance tool (DCAT) and to investigate its impact on the mutual understanding between refugee patients and their German general practitioners (GPs). In the first study phase, an action-oriented approach is used to implement DCAT. In the second study phase, DCAT use will be evaluated with a mixed methods design.

The main outcome assesses the re-consultation rates of patients before and after using DCAT. Secondary outcomes include the usability of the tool, its acceptance and perceived quality by patients, the accuracy of the information collected as determined from analysing the reasons for the consultation (ICPC-2 codes), and diagnosis (ICD-10 codes). The acceptance by patients, socio-demographic factors and native language are also taken into account.

The research designs for both study phases include questionnaires, semi-structured interviews, non-participant observation and analysis of collected patients’ data.

All the collected data is pseudonymised.

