As a secondary outcome, the following are to be assessed:The perceived quality of the communication in the consultation by both patients and healthcare professionals. After each consultation patients are asked to fill in questionnaires about their perceptions around mutual understanding with the attending physician.The perception of the usability and acceptance of the tool by patients and GPs, which is also gauged through questionnaires after each consultation.The usability and acceptance of DCAT by different patient subgroups according to age, gender, country of origin, asylum status, educational level and spoken languages. When patients decide to stop using DCAT, this will also be registered.The accuracy of collected information through DCAT. The aim is to clarify whether DCAT can be reliably utilised and incorporated into the clinical decision-making process to improve healthcare outcomes [20, 21]. DCAT estimates the reasons for the encounter as ICPC-2 codes based on the information provided by the patient, and doctors will also be indicating their diagnosis (ICD-10 codes). We want to compare the DCATs estimated reasons for a consultation and the GP’s diagnosis in terms of plausibility and contingency to investigate the accuracy of the provided medical information by DCAT [22]. Also, GPs will be asked after each consultation through questionnaires if their impression of the patient’s description contradicts the information provided by DCAT.

For a deeper insight into the acceptance of DCAT users, we will apply qualitative research methods, namely:Use of open and partially standardised interviews conducted with healthcare workers (GPs and nurses) and a group of selected patients in the refugee camp.The researchers also will explore the use of DCAT as a non-participant observer.

The research design of the DCAT Study is shown in Fig. 1.

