**Acceptance, usability, quality of communication, accuracy of DCAT information, and presence of ad-hoc (lay) interpreters**

When a patient finishes entering his/her data on DCAT, a digital questionnaire follows to assess patients’ experiences with DCAT (see Additional file 1). This questionnaire consists of two parts, the first consists of four questions and is applied directly after using DCAT. These questions seek to evaluate the acceptance and usability of DCAT. The final question regards the educational level of the patients.

The second section of the patient questionnaire follows after the consultation. It has five questions, which focus on the impact of using DCAT in the consultation situation, especially the communication and mutual understanding between the healthcare providers and the patients.

The attending physicians at the Friedland primary healthcare centre are asked to give their feedback on each consultation also using a two-part questionnaire (see Additional file 2). The first section comprises three questions, which ask the doctors their opinions on the perceived quality of communication and mutual understanding throughout the consultation. Whether ad-hoc interpreters are present is also documented. The second set of questions follows only when a medical report (synopsis) is produced through DCAT (see Additional file 3) and asks whether this printed report influences the consultation. Also, any inconsistencies between the DCAT collected information and clinical impressions of the doctors are sought.

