### Data analysis

The quantitative data will be analysed using SPSS (version 25.0) on the basis of descriptives (i.e., frequencies and means). Differences between patients of the study group and the control group will be tested for statistical significance. Furthermore, differences between patients using DCAT and their physicians regarding their opinions on the perceived quality of communication and mutual understanding throughout the consultation will be tested for significance.

The qualitative data (interviews with GPs, nurses and patients) will be audio-recorded. Two members of the team will code the interview transcriptions and analyse them by the summarising qualitative content analysis [31].

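### The only patient–physician analysis named is a test for a difference in ratings. It should be joined by a paired agreement measure, and non-significance must not be read as agreement.

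*Protocol article*

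**What the plan says.** The abstract gives as one aim "to investigate its impact on the mutual understanding between refugee patients and their German general practitioners". Among the secondary outcomes in the Design section is "The perceived quality of the communication in the consultation by both patients and healthcare professionals".

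Both sides supply ratings. For patients, Design says: "After each consultation patients are asked to fill in questionnaires about their perceptions around mutual understanding with the attending physician". For physicians, the part of Quantitative measurements that describes the questionnaires has a first section of three questions, "which ask the doctors their opinions on the perceived quality of communication and mutual understanding throughout the consultation", answered for each consultation.

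The Data analysis section then plans three things for the quantitative data: a description by frequencies and means, a significance test between study and control group, and a comparison of DCAT users with their physicians. The last is a significance test of the "differences between patients using DCAT and their physicians regarding their opinions on the perceived quality of communication and mutual understanding". No specific test and no measure of agreement is named.

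**The concern.** The two ratings come from the same consultation, so the data can show how often the two people in the room judged it alike. A test of difference does not use that information. It compares the overall level of the patients' ratings with that of the physicians' ratings. Patients who rate a consultation good where the physician rates it poor can be balanced by the reverse elsewhere, and the test then finds nothing.

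Both possible results are open to misreading. A non-significant result may be taken to mean that patients and physicians agree. A significant result may be taken to mean that they disagree in a way that matters, although the difference is small and most pairs are identical. The comparison bears on a stated aim of the study, so it is worth making it informative.

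**Working it through.** The article gives no figure for this comparison, so there is nothing of its own to reproduce. The check has two parts.

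**Inputs**
- DCAT group: 440 patients, dropout 10% (Sample size calculation). 440 × 0.90 = 396 patients, taken as one rated consultation each.
- Two-sided significance level 5%. The article states it for the primary outcome; it is assumed here for this comparison.
- Power 80%: assumed, as the article states none.
- Rating scale 1 to 5: assumed, as the questionnaires are not shown.

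**1. How small a difference is detectable**

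For n independent pairs, detectable mean difference in SDs of the paired differences = (1.96 + 0.84)/√n = 2.80/√n.
- n = 440: 2.80/20.98 = 0.13 SD.
- n = 396: 2.80/19.90 = 0.14 SD.

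**2. What the test does with known agreement (396 constructed pairs)**

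*(a) Mirror-image ratings.* Patients rate 1, 2, 4 and 5, 99 times each; the physician gives 6 minus the patient's rating.
- Means: 3.00 and 3.00. Paired t-test p = 1.00; Wilcoxon signed-rank p = 1.00.
- Exact agreement: 0%. Pairs differing by one or more categories: 100%.
- Quadratic-weighted kappa = 1 − (observed mean squared difference)/(that expected by chance). Observed: half the pairs differ by 4 and half by 2, so (16 + 4)/2 = 10. Expected: twice the variance of the ratings, 2 × (4 + 1 + 1 + 4)/4 = 5. Kappa = 1 − 10/5 = −1.00.

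*(b) Near-identical ratings.* 40 of 396 physician ratings are one point above the patient's; the other 356 are equal.
- Means: 3.00 and 3.10. Mean difference = 40/396 = 0.101.
- SD of differences = √(0.101 × 0.899 × 396/395) = 0.302. SE = 0.302/19.90 = 0.0152. t = 0.101/0.0152 = 6.7, p = 9 × 10⁻¹¹; the Wilcoxon p is 3 × 10⁻¹⁰.
- 95% CI for the mean difference: 0.101 ± 1.97 × 0.0152, that is 0.07 to 0.13 points.
- Exact agreement: 356/396 = 90%. Pairs differing by one or more categories: 10%. Weighted kappa 0.975.

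| | Difference test | Exact agreement | Weighted kappa |
|---|---|---|---|
| (a) Mirror image | p = 1.00 | 0% | −1.00 |
| (b) 40 pairs shifted by one point | p = 9 × 10⁻¹¹ | 90% | 0.975 |

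The p-value runs opposite to the agreement. The rank test gives the same picture as the t-test, so the limitation does not depend on comparing means. Both data sets are extremes built to show the mechanism; they do not predict the trial's ratings.

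**The case against.** The strongest reply is that the article does not make the claim that would be wrong. Nowhere does it say that a non-significant difference will be taken as agreement or as proof of mutual understanding. Whether one side rates systematically higher is a legitimate question, and a difference test answers it. That stands.

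A reader might go further and infer that the planned analysis cannot address mutual understanding at all. The documents do not support this. Mutual understanding is something each side is asked to rate, so the planned frequencies and means already carry information on it. Agreement alone would not establish it either: if both parties rate understanding as poor, they agree perfectly. Kappa is therefore an addition to the level of the ratings and not a replacement for it.

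A reader might also infer that patients and physicians would be analysed as two independent groups. The article does not say so. It refers to the patients' own physicians, which is compatible with pairing, and the choice of test may stand in a fuller analysis plan that is not shown.

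Finally, it is tempting to count 440 × 2.65 = 1,166 pairs and argue from a still smaller detectable difference. But 2.65 is the consultation rate from before the study, and the count assumes no dropout, complete questionnaires and independent repeat visits. Only the scale of one pair per patient is safe.

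What remains is narrower. The published text fixes the target of its one named patient–physician analysis as a difference, and a difference is not agreement.

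**Conclusion.** The point holds as a suggested improvement to a secondary analysis. The named test tells whether one side rates higher; it does not tell whether patient and physician judged the same consultation alike, and its p-value should not be read as if it did. With 396 to 440 pairs, a mean difference of 0.14 to 0.13 SD of the paired differences is detectable with 80% power, so a significant result needs its size shown.

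This rests on one fully rated consultation per patient, a two-sided 5% level, 80% power and independent pairs. The last is a simplification, because six GPs supply all the physician ratings. The remedy presumes that at least some items are put to both parties on a common scale, which cannot be confirmed without the questionnaires. The primary outcome is not affected.

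**What to change.** In Data analysis, extend the sentence on patients and physicians. For each item asked of both parties on the same scale, match the two ratings by consultation and report:
- the cross-table of patient by physician rating;
- the share of pairs that differ by one or more categories, and weighted kappa, each with a 95% CI;
- the paired mean difference with its 95% CI;
- the level of each side's ratings, so that shared good ratings can be told from shared poor ones.

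Use one consultation per patient, chosen by a rule fixed in advance, or intervals clustered by patient. State that a non-significant difference will not be interpreted as agreement. Items without a counterpart on the other questionnaire stay descriptive.

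Cost: a few sentences and slightly more analysis work on the same data, provided that the patient and physician forms can be linked by consultation.

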## Discussion

While previous research has focused mostly on investigating the efficacy of interpreters and translators’ services to overcome language barriers in healthcare settings [32, 33], only some studies have evaluated the application of digital interpretation tools consistently at a primary healthcare level and its effects on health outcomes [13, 34]. Therefore, our study aims to assess the new DCAT in an action-oriented approach with mixed methods design. It ensures not only the involvement of patients but also different healthcare professionals (GPs and nurses). By following this approach, we reduce the limitations of previous research that focuses on only one aspect (either the patients or the healthcare providers) [35]. In addition, this study will provide new insights into the possible future benefits of DCAT in a primary care setting.

Earlier, past studies have had the tendency to evaluate the use of interpreters as a gold standard for dealing with the communication gap, especially in communities with high migration background [26, 32]. However, some recent studies have pointed to the limitations and restrictions of using interpreters and translators on a wide scale [33, 34, 36]. One of the key issues is patient confidentiality, which might be at risk if a third party is involved during the medical consultation [33, 35]. One of the many advantages of DCAT is that no third person is needed, which ensures the privacy of the patient’s personal and medical information.

By integrating different research methods, we expect to obtain a deeper understanding of the healthcare provider and patient perceptions. Indeed, Day et al. showed that following this approach for assessing such applications has better outcomes in terms of clinical settings [37].

During times when there are insufficient numbers of professional interpreters available to meet high numbers of patients (e.g. the 2015 refugee crisis in Europe), DCAT may represent a solution [38–40]. The need to develop practical solutions to facilitate communication for this group of patients during healthcare encounters is increasing especially after the unprecedented number of refugees and asylum seekers globally [16, 41]. Bischoff et al. have shown that language barrier costs are higher for healthcare provision among refugees and asylum seekers [10].

It should be noted however that DCAT is neither able to make a diagnosis nor can it give medical advice. It is an aid for doctors to obtain the medical history (symptoms and signs) from the patient perspective without the need for interpreters and translators.

We do expect some possible challenges with our study design. As this digital communication assistance tool is newly developed and its adoption will likely change the daily routine at the medical consultation, we are expecting some reluctance to use it, especially on the part of the healthcare provider. Such potential difficulties may require additional DCAT revisions during the study to ensure the quantitative as well as qualitative research goals (extension of the initial 18 month study period, changing the locations, where the patient can use DCAT, changing routine, e.g. admission times).

We also anticipate that not all patients will utilise DCAT because of unfamiliarity with the technology involved or the unavailability of some spoken languages at the primary healthcare centre in Friedland. During the study period, we will find out about such possible limitations and obstacles that might prevent DCAT usability.

In conclusion, this study remains an essential step to assess the potential effectiveness of the DCAT tool in facilitating communication and removing language barriers to improve the quality of the healthcare encounter for patients who do not speak German.

## Abbreviations

AsylBLG: Asylbewerberleistungsgesetz (Services for Asylum Seekers Act)
DCAT: Digital communication assistance tool
GPs: General practitioners
ID: Identification card
